### Study design

The study is designed as a cluster-randomized controlled trial, incorporating qualitative analysis. The qualitative analyses have been used during intervention development and piloting. Further qualitative methods will be applied to perform a process evaluation of the randomized trial and to assess the acceptance of the interprofessional Medication Therapy Management approach [33]. The study design is developed in line with the CONSORT statement extension to cluster RCT [34, 35]. The cluster design is chosen to avoid spillover effects across patients of the control and intervention groups. To ensure the feasibility and a high acceptance of the methodical cornerstones of the study, its essential aspects were piloted. Thereby the patients recruiting process, randomization routines, the applied documentation forms and data collection procedures are examined.

Participating GPs are allocated to one of three study arms by undertaking a cluster randomization on the level of the primary care units following a Stepped Wedge Design [36]. In this sense all GPs are initially assigned to the control group. After a 6 month observation period, general practitioners are randomly allocated to one of the three groups and the interprofessional Medication Therapy Management approach is implemented sequentially per each group with a lag of 3 months (see Fig. 1).

**Fig. 1 Fig1:**
[figure not shown]
Design of the WestGem-study. This figure shows design and timeframe of the WestGem-study

Patients recruited by the GPs receive standard care during the control period. After the implementation of the MTM-approach a first comprehensive Medication Review is performed by the pharmacists as well as a support by the home-care specialists using case management techniques (see Table 1). The Medication Review and the personal support by the home-care specialists are repeated after 6 months. The GP is free to accept or deny any suggestions made by the pharmacists and health-care specialists and keeps his or her unrestricted individual freedom of choice at all time during the study period. Primary and secondary endpoints are assessed at baseline and 3, 6, 9, 12 and 15 months post-baseline. Patient groups are compared with respect to their treatment response within the study period.

**Table 1 Tab1:** Components of the intervention and training strategy for its implementation. This table summarizes the components of the intervention and planned training strategies

Components of intervention and implementation		Content	Participants
*Intervention*	I. Transfer of medical patient data	Information concerning diagnosis, patient’s medication, quality of life, mobility, risk of failing, allergies	GP
	II. Assessment at patients site	Brown bag review and collection of information concerning side effects, adherence, social support and else	Home-care specialist, patient
	III. Anonymised data transfer to pharmacist	Assessment data	Home-care specialist
	IV. Medication review and SOAP note	Assessment of pharmacotherapy, generation of a new medication plan, suggestions for monitoring and patient counseling	2 Pharmacists per patient (one pharmacist generates a first draft of the SOAP note, second one reviews suggested plan)
	V. Transfer of the SOAP note to home-care specialist	SOAP note and advices addressing home-care specialist tasks	Pharmacist
	VI. Information of GP	SOAP note with new medication plan, home-care specialist’s note for the GP (concerning for example home-care devices)	Home-care specialist
*Training concept for implementation*	I. Kick-off meetings	Information concerning organizational aspects, process’s time frame, controlling tools, assessment instruments	Home-care specialists, pharmacists, GPs and moderators
	II. profession-specific trainings	Training in medication therapy management, medication review and SOAP-writing	Home-care specialists, pharmacists, and moderators
		Training in case management	
	III. training in patient assessment	Assessment instruments, case studies	GPs and moderators
	IV. Process controlling	Ongoing feedbacks on process performance (e.g. accepted interventions, time frame)	All participants

### Primary hypothesis

It is proposed that patients receiving the interprofessional MTM show a significantly lower MAI score compared to patients receiving standard care [25, 26]. Therefore the study evaluates the primary null hypothesis that an interprofessional Medication Therapy Management approach has no influence on the quality of drug therapy.

### Randomization

Participating clinics were randomly allocated to one of three study arms. A biometrician who is not involved in the field work, randomly selects the clinics. To avoid changes in physician’s prescription behavior, random lists remain concealed until each allocation date.

### Study population

#### Patient recruitment

The recruitment of the patients is carried out by the participating GPs. To avoid selection bias, patients’ inclusion comprises of two steps. At first, all patients are screened for the defined in- and exclusion criteria. GPs systematically identify patients who are generally eligible for study inclusion. Potential study patients are listed in alphabetic order and are numbered consecutively (basic population). In a second step GPs add gender, age, and conditions (diagnoses) to this list. At a later date physicians provide a pseudonymous version of the recruitment list to the biometricians who determine a random sample of patients. These participants are informed about the study by their GP and asked to participate. After giving informed consent, baseline documentation forms and questionnaires are completed. For every patient of the sample list who declines participation, a new patient is drawn from the basic population pool. For potential study patients who decline participation a sensitivity analysis is planned at the end of the trial to determine whether this sample differs according to age, gender and structure of acute, as well as chronic conditions.

Figure 2 illustrates the flowchart for recruitment of primary care units and patients.

**Fig. 2 Fig2:**
[figure not shown]
CONSORT flowchart of recruitment of practices and patients (projected). This figure illustrates the projected recruitment flowchart of the WestGem-study

#### Inclusion and exclusion criteria

The following inclusion criteria are defined:patients age ≥ 65 years,at least 3 chronic diseases out of two organ systems with one being a cardiovascular disease (for the identification of relevant chronic diseases the list published by van den Bussche et al. 2011 was used [37]),at least 1 visit to the Primary Care Provider in each of the last 3 quarters,at least 5 chronic systemic available medications,(signed informed consent).

Patients with an insufficient ability to speak or read German, participation in other studies at the present time and with the existence of severe illnesses that might be lethal within 12 months according to the GP’s judgment are excluded.

#### Sample size and power calculation

Sample size calculation for the stepped wedge design is based on Woertman et al. [38]. Because there were no studies investigating the effect of Medication Management an effect size of 0.25 is considered as clinically and socially relevant. Based on this assumption and using a two-tailed *t*-test with statistical power of 80 % and significance level alpha = 0.05 a total unadjusted sample size of *N* = 502 is needed. An assumption of 20 patients per practice and little correlation between the clusters (ICC = 0.05) leads to a design factor of 0.383 in the present step wedge model. Adjusting the sample size with the design factor and considering a maximum drop-out rate of 20 % the final sample size is calculated to *N* = 240.

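### The design factor of 0.383 does not match the six-occasion schedule; by the plan's own method the factor is 0.68, and N = 240 gives about 56% power, not 80%

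*Protocol article*

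**What the plan says.** In the Protocol article, Sample size and power calculation starts from a standardised effect: "an effect size of 0.25 is considered as clinically and socially relevant". A two-tailed t-test with 80% power and "significance level alpha = 0.05" gives an unadjusted total of 502. With 20 patients per practice and an ICC of 0.05, the section says this "leads to a design factor of 0.383 in the present step wedge model". After a 20% drop-out allowance the total is 240. The section does not print the number of baseline occasions or of occasions per step behind the factor.

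The schedule is given elsewhere. Under Study design, practices are randomised to three groups after a 6-month observation period, and the intervention is "implemented sequentially per each group with a lag of 3 months". The text below Fig. 1 states: "Primary and secondary endpoints are assessed at baseline and 3, 6, 9, 12 and 15 months post-baseline". Data collection and Primary outcome repeat these six time points for the MAI, labelling the first one t0/t1.

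**The concern.** A stepped-wedge design factor depends strongly on how many measurements each practice contributes, and above all on how many fall between successive crossovers. Here crossovers and assessments are both 3 months apart, which leaves one measurement per step. A factor as low as 0.383 looks too small for that.

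The rest of the calculation is multiplication, so the whole claim of 80% power at 240 patients rests on this one number. If it is too favourable, a non-significant primary result would be read as evidence against a 0.25 SD effect with more confidence than the calculation supports.

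**Working it through.** **Inputs.** From the sample size section: effect 0.25 SD, two-sided alpha 0.05, power 80%, unadjusted N = 502, n = 20 per practice, ρ = 0.05, drop-out 20%. From Study design: k = 3 steps, 3 months apart. From the text below Fig. 1: occasions at 0, 3, 6, 9, 12 and 15 months.

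**The plan's own figure.** 502 × 0.383 = 192.3 evaluable, and 192.3 / 0.8 = 240.3. The arithmetic is right once 0.383 is accepted. The 502 is also fair: a normal approximation gives 504 and an exact t calculation 506.

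**Formula.** With b baseline occasions and t occasions per step, the closed-form stepped-wedge design factor is

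DE = [1 + ρ(ktn + bn − 1)] / [1 + ρ(ktn/2 + bn − 1)] × 3(1 − ρ) / [2t(k − 1/k)].

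A generalised least squares variance for a model with fixed time effects and a random practice intercept, derived separately, gives the same values.

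**Where 0.383 comes from.** A search over k = 2 to 12, b = 0 to 7 and t = 1 to 6, with n = 20 and ρ = 0.05, finds one match: k = 3, b = 3, t = 2.

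- First fraction: (1 + 0.05 × 179) / (1 + 0.05 × 119) = 9.95 / 6.95 = 1.432
- Second fraction: 2.85 / (4 × 2.667) = 0.2672
- DE = 0.3825, and 502 × 0.3825 / 0.8 = 240.0

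That layout has 3 + 3 × 2 = 9 occasions.

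**The schedule as described.** With k = 3, b = 3, t = 1 (6 occasions):

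- First fraction: (1 + 0.05 × 119) / (1 + 0.05 × 89) = 6.95 / 5.45 = 1.275
- Second fraction: 2.85 / (2 × 2.667) = 0.5344
- DE = 0.6815

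The least squares calculation gives 0.6815 whether the first crossover comes after occasion 1, 2 or 3, so the result does not need Fig. 1.

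**Other readings.**

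| Layout | Occasions | DE | N incl. drop-out | Power at 192 |
|---|---|---|---|---|
| b = 3, t = 2 (reproduces 0.383) | 9 | 0.383 | 240 | 80% |
| b = 3, t = 1 (as described) | 6 | 0.682 | 428 | 56% |
| t0 and t1 counted separately, t = 1 | 7 | 0.659 | 413 | 57% |
| b = 1, t = 2 (contradicts the 3-month lag) | 7 | 0.429 | 269 | 75% |
| b = 2, t = 2 (contradicts the 3-month lag) | 8 | 0.402 | 252 | 78% |

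With k = 3 and t = 1 the first fraction always exceeds 1, so DE cannot fall below 0.534 however many baseline occasions are added.

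**Size of the shortfall by the plan's method.**

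- Required: 502 × 0.6815 = 342 evaluable; 342 / 0.8 = 428.
- Power with 192 evaluable: Φ(0.25 / √(4 × 0.6815 / 192) − 1.96) = Φ(0.14), about 56%. Using 16 evaluable patients per practice (DE = 0.675) also gives 56%.
- Effect detectable with 80% power at 192: (1.96 + 0.84) × √(4 × 0.6815 / 192) = 0.33 SD.
- With the 165 patients named in the abstract, power is about 49% before any drop-out.

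**Allowing for the closed cohort.** The formula treats repeated scores from one patient as independent, given the practice. Adding a patient random effect (12 practices, 16 evaluable each, ICC 0.05, six occasions) gives the power below. The correlations are assumptions, since the protocol states none.

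| Assumed correlation | 0.3 | 0.5 | 0.7 |
|---|---|---|---|
| Read as total within-patient correlation | 68% | 82% | 96% |
| Read as patient share of within-practice variance | 70% | 83% | 96% |

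Power reaches 80% at a total within-patient correlation of about 0.48.

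**The case against.** The strongest reply is that 56% is not the trial's real power. The MAI is scored every 3 months on the same patients, who take at least five chronic medicines, so a within-patient correlation of 0.5 or more is plausible. In that case 240 patients would reach or exceed 80%. This stands: the check shows that the stated derivation does not support 80%, not that the trial is underpowered. It does not rescue the section, because the calculation neither states nor uses such a correlation, and the printed factor still contradicts the printed schedule.

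A second point is that the nine-occasion origin is a back-calculation. The inputs are not printed, and the match is unique only with n held at 20. That is also true, but the error does not depend on where 0.383 came from. No reading of three steps with one occasion each gets below 0.534.

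Third, the article condenses a fuller protocol, and the Statistical analyses section does not exclude a patient-level effect in the mixed model. The absence of such a term is therefore not counted as an error here.

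Finally, data collection is complete according to Trial status, so nothing in the conduct can change. That limits the remedy to the text, but the text is what readers will use to interpret the result.

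**Conclusion.** The concern holds. For three groups crossing over 3 months apart with six 3-monthly assessments, 20 patients per practice and ICC 0.05, the factor is 0.68 (0.66 if t0 and t1 are separate occasions). The printed value is too favourable by a factor of 0.6815 / 0.383 = 1.8. Under the plan's own method, the stated 80% power at N = 240 becomes about 56%.

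This rests on the stated n, ICC, effect and drop-out, and on one measurement per step, which the text fixes. Power under a cohort model may lie on either side of 80%, depending on a within-patient correlation that the calculation leaves out.

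**What to change.** In Sample size and power calculation:

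1. Replace 0.383 with the factor for the actual layout, and print the number of steps, baseline occasions and occasions per step used.
2. Recompute power for the closed cohort with a patient-level correlation, stating how that correlation is defined and that it is assumed.
3. Report power over a range, for example 0.3 to 0.7, in place of the single figure of 80%.

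If a nine-occasion design really was planned at the time, say so and reconcile it with the schedule in Study design.

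The cost is one recalculation and a corrected paragraph. No patients, visits or changes to the primary analysis are requested. The price is that stated power becomes lower, or conditional on an assumption.

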### Data collection

The main data collection comprises of paper-pencil questionnaires and documentation forms for chart reviews as well as telephone interviews with patients. After obtaining written informed consent, patients are registered in the study coordinating center of the Department of Health Care Management and Public Health Wuppertal (Germany).

Patients are asked to fill in a questionnaire. GPs document additional data from patients’ chart and assess the current clinical status of the patient (e.g. blood pressure, Tinetti test, mini-mental state examination).

Patient questionnaire, chart review and telephone interview are performed at baseline (t0/t1), 3 months post-baseline (t2), 6 months (t3), 9 months post-baseline (t4), 12 months post-baseline (t5) and 15 months post-baseline (t6). The baseline documentation includes a retrospective assessment period over six month.

The pharmacists’ and home-care specialists’ assessment and reporting instruments are evaluated to gain the following information:medication appropriateness index (MAI) [25, 26];medication regimen complexity index (MRCI) [27];potential inadequate medication,drug related problems,possible medical interactions,number of taken over-the-counter medication,deviation between the GPs prescribing and the brown bag,patient’s therapeutic goals,experienced side effects andfurther interventions suggested during Medication Review.

Within semi-standardized and guideline-based telephone interviews GPs are interviewed twice (at the beginning and at the end of study) to discuss their expectations toward and experiences with the interprofessional Medication Therapy Management approach. To gain influencing factors on physician and study site level, a standardized questionnaire is used that was developed in a previous study [39].

### Outcome measures

#### Primary outcome

The primary objective of this study is to determine whether the complex intervention can change the quality of medication therapy. Therefore specialised study pharmacists measure the quality of medication therapy at baseline (t0/t1), 3 months post-baseline (t2), 6 months (t3), 9 months post-baseline (t4), 12 months post-baseline (t5) and 15 months post-baseline (t6) by applying the MAI, a validated instrument with good intra-rater and inter-rater reliability, as well as face and content validity [40, 25, 41, 26].

The MAI is an implicit (judgment-based) process measure, which assesses ten elements of prescribing: indication, effectiveness, dose, correct directions, practical directions, drug-drug interactions, drug-disease interactions, duplication, duration and cost. To standardize the rating process, the index has operational definitions and instructions. The ratings result in a weighted score that serves as a summary measure of prescribing appropriateness [25, 26, 22]. We assume that an increase in appropriate polypharmacy would improve indicators of morbidity such as reduction in adverse drug events (ADEs) or hospital admissions, which are both also followed in this study. Furthermore we suggest that appropriate prescribing would positively influence mortality as well as morbidity and quality of life.

The choice for the process measure MAI as primary outcome parameter was made in consideration of a current Cochrane review [42] determining, which interventions are effective in improving the appropriate use of polypharmacy, reducing medication-related problems in older people and avoiding hospital admissions. The review reported that the majority of the eligible studies (seven out of eleven) used the validated MAI as a primary outcome. To determine whether the MAI can predict patient relevant outcomes and to assess its predictive validity, additional analyses are planned. More specifically, it will be examined whether any changes in the primary outcome measure result in changes in the secondary outcomes.

#### Secondary outcomes

Additional information regarding the quality of medication therapy will be obtained from assessment instruments used by the study pharmacists within their Medication Review. These documents includethe number of drug related problems, classified according to PCNE version 6.2,medication complexity, measured by the medication complexity index (MRCI) [27],the prevalence of inadequate medication, using the PRISCUS-list [2] for assessment (see Table 2).

**Table 2 Tab2:** Outcome parameters and instruments. This table displays the outcome parameter of the study as well as instruments

Outcome parameter	Instrument	Data source
Primary outcome		
Quality of medication therapy	Medication Appropriateness Index (MAI)	PHARM
Secondary outcomes		
Sociodemographic data	Items from German standard questionnaire [47]	CRF, TI
Laboratory data	Patient chart	CRF
Diagnosis	Patient chart (ICD-10)	CRF
Allergies	Patient chart	CRF
Comorbidities	Cumulative Illness Rating Scale Geriatric Version (CIRS) [48]	CRF
Reported side effects	Self-developed item	CRF, TI
Quality of Life	EuroQol (EQ-5D) [49], Short Form 12 Health Questionnaire (SF-12) [50]	PQ, TI
Depression	Patient Health Questionnaire (PHQ9) [51]	PQ
Activities of daily living	ADL, iADL [52, 53]	TI
Risk of falling	Tinetti-Test [54]	CRF
Mobility	FFB-Mot [55]	TI
Cognitive status	Adopted Mini-Mental State Examination (MMSE)	CRF
Pain	German Chronic Pain Scale [56]	PQ, TI
Self-rated health	Self-developed item	PQ
Vision and hearing	Self-developed item	TI
Health behavior (smoking, drinking)	Self-developed item	PQ, TI
Social participation	F-SOZU K14 [57]	TI
Prescribed medication	Patient chart	CRF
Brown bag medication	Self-developed assessment instrument	HCS
Healthcare utilization and costs	Data from inpatient and outpatient care, rehabilitation, medical devices, etc.	CRF
Complexity of medication	Medication regimen complexity index (MRCI) [27]	PHARM
Adherence	MARS, MORISKY [25, 26]	TI
Drug-related Problems	Classification according PCNE version 6.2	PHARM
Inadequate medication	Potentially inadequate medication (German PRISCUS-list) [2]	PHARM
Patients goals of therapy	Self-developed assessment instrument	HCS
Difficulties in medication handling	Self-developed assessment instrument	HCS
Nutrition	Self-developed assessment instrument	HCS
Dizziness	Self-developed assessment instrument	HCS
Mortality	Patient chart	CRF
Accepted medication proposals	Self-developed item	CRF
Additional parameters		
Barriers of concept implementation	Qualitative research approach	TI, FG
Practice characteristics	Self-developed questionnaire [39]	TI, on-site monitoring

*PHARM* pharmacists, *HCS* home-care specialist, *PQ* patient questionnaire, *CRF* case report form, *TI* telephone interview, *FG* focus groups

Data according to over-the-counter medication, drugs prescribed by specialists, reported side effects, patients goals of therapy, patient reported medication and the risk of falling are provided by the assessment instrument of the home-care specialists.

The medication adherence is determined according to Morisky and MARS. Health related quality of life is assessed using the Short Form 12 Health Questionnaire (SF-12) and the EuroQoL instrument EQ-5D. We are documenting these instruments using a paper-based patient questionnaire as well as during the telephone interviews. Discrepancies between the two measures will be analysed.

Other secondary outcome parameters are: depression (PHQ-9), self-rated health, activities of daily living (ADL/iADL), mobility (FFB-Mot), pain (GCPS), mortality, hospital admissions, number and type of accepted medication proposals, social participation (F-SOZU K14), health care utilization and total healthcare costs.

Additionally quantitative (process documentation instruments) and qualitative (focus groups, narrative interviews) process evaluation is conducted to identify possible barriers of implementation and to detect needs to modify the intervention.

### Statistical analyses

Baseline and demographic characteristics are analysed descriptively (number of valid cases, mean, standard deviation, minimum, median, lower and upper quartile, maximum for quantitative variables and number and proportions for qualitative variables).

The statistical analyses of the full-analysis set will follow the intention-to-treat (ITT) principle. This dataset includes all trial subjects who are randomized, meet all inclusion and exclusion criteria, have signed informed consent and have at least a baseline MAI score. Supportive analyses will be performed for the per-protocol (PP) population that includes all trial subjects of the ITT set who were treated as randomized and have at least two MAI scores after changing from control to intervention.

The primary hypothesis will be evaluated by a mixed model with treatment group and time as fixed effects and clustering structure as random effect. Significance level is set to alpha = 5 % (two-sided). It is assumed that values are missing at random (MAR) therefore no values need to be replaced in the mixed model. Secondary outcomes are analysed analogously. Further analyses are performed exploratory. In the sensitivity analysis missing values are replaced with last observation carried forward (LOCF).

Subgroup analyses will be performed with respect to age, gender, migrant status, social bonding and complexity of morbidity structure.

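### The LOCF sensitivity analysis carries control MAI scores across the one-way crossover, so it shrinks the effect by design and is a poor test of the MAR assumption

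*Protocol article*

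**What the plan says.** All points are from the protocol article.

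- **Missing data (Statistical analyses).** For the primary model: "It is assumed that values are missing at random (MAR) therefore no values need to be replaced in the mixed model". For the sensitivity analysis: "In the sensitivity analysis missing values are replaced with last observation carried forward (LOCF"). The article names no other method for missing MAI scores. The sensitivity analysis under Patient recruitment compares patients who decline to take part, and the per-protocol set is a different population.
- **Model (Statistical analyses).** A "mixed model with treatment group and time as fixed effects and clustering structure as random effect".
- **Analysis set (Statistical analyses).** Besides eligibility and consent, randomised patients need only "have at least a baseline MAI score", so a patient with a single control score stays in.
- **Design (Study design).** "In this sense all GPs are initially assigned to the control group"; the intervention is then "implemented sequentially per each group with a lag of 3 months" between three groups. "Primary and secondary endpoints are assessed at baseline and 3, 6, 9, 12 and 15 months post-baseline".
- **Expected direction (Primary hypothesis).** Intervention patients should "show a significantly lower MAI score compared to patients receiving standard care".

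**The concern.** LOCF assumes that a patient's score stays where it was last seen. In a parallel-group trial the carried value at least belongs to the patient's own arm. Here the arm changes during follow-up, always in the same direction. A patient whose last MAI precedes the switch contributes a control score to every later intervention visit, and the opposite error cannot occur. Patients lost after the switch carry intervention scores, so the problem lies with those lost before it.

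If the intervention works, the LOCF estimate is therefore expected to be smaller than the primary one even when MAR is true. A reader who sees the two differ could take this as evidence of informative drop-out when the calendar of crossovers explains it. The analysis meant to probe the MAR assumption would then mislead about it.

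**Working it through.** **Inputs from the article.** Three groups at 3-month lags; six occasions (0, 3, 6, 9, 12, 15 months); effect 0.25 SD, ICC 0.05, 20 patients per practice and at most 20% drop-out (Sample size and power calculation); 12 practices (Abstract).

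**Assumptions of mine.** Drop-out is monotone, equal across groups, spread evenly over the five intervals (4% each) and unrelated to outcome. The effect is constant. The patient-level share of variance is 0 to 0.6. Fig. 1 is not available and the text does not fix the first exposed visit, so three schedules are shown.

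**The plan's own figure.** 502 × 0.383 = 192.3, and 192.3 / 0.80 = 240.3, which matches the stated 240. So 20% is the loss the plan budgets for. The article gives no figure for the LOCF analysis itself.

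**Step 1: share of intervention-period values that are control scores.** Number the visits 0 to 5. If a group's first exposed visit is s, a fraction 0.04 × s is lost before it, and LOCF fills all 6 − s exposed visits of those patients with a control score. The share is Σ 0.04·s·(6 − s) / Σ (6 − s):

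- 3/6/9 months (s = 1, 2, 3): (0.04×5 + 0.08×4 + 0.12×3) / 12 = 0.88 / 12 = 7.3%
- 6/9/12 months (s = 2, 3, 4): (0.08×4 + 0.12×3 + 0.16×2) / 9 = 1.00 / 9 = 11.1%
- 9/12/15 months (s = 3, 4, 5): (0.12×3 + 0.16×2 + 0.20×1) / 6 = 0.88 / 6 = 14.7%

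A constant hazard per interval, 1 − 0.8^(1/5) = 4.4%, gives 7.8%, 11.6% and 15.0%.

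**Step 2: effect on the estimate.** The expected LOCF mean of group g at visit t is Σ_j P(last visit = j) · μ_g(min(j, t)). Passing these means through the generalised least squares estimator (ΣX′V⁻¹X)⁻¹ ΣX′V⁻¹y, with occasion and exposure fixed and practice and patient random, gives:

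| First exposed visits (months) | LOCF estimate / true effect, 4% per interval | Same, constant hazard |
|---|---|---|
| 3/6/9 | 0.914 to 0.909 | 0.909 to 0.904 |
| 6/9/12 | 0.885 to 0.881 | 0.880 to 0.877 |
| 9/12/15 | 0.856 to 0.854 | 0.852 to 0.850 |

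The ranges cover patient-level shares of 0 to 0.6. With the Abstract's 165 patients (165 / 12 = 13.75 per practice), the ratios move by less than 0.003. A common linear time trend leaves them essentially unchanged. If all 20% were lost straight after baseline, the ratio would be exactly 0.80 under every schedule.

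**Step 3: is it LOCF or the missingness?** In simulation (1,500 runs per schedule, true effect −0.25 SD, constant hazard), the mixed model on observed data averaged −0.251, −0.251 and −0.250. LOCF averaged −0.227, −0.219 and −0.212. The Monte Carlo standard error was about 0.002. The missingness is harmless and the carrying forward causes the shrinkage.

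**Step 4: no true effect.** With equal drop-out across groups the LOCF bias is 0, also with a linear time trend. With unequal drop-out and a trend of 0.05 SD per visit it was at most 0.004 SD, in either direction.

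**Which schedule?** The text fits first exposed visits at 3/6/9 months best:

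- Trial status dates delivery and outcome collection to the same 15 months, directly after baseline.
- Data collection describes the baseline as covering six retrospective months, which can serve as the 6-month observation period.
- The per-protocol set needs two MAI scores after the switch. Under 9/12/15 the third group has only one.
- The medication review is repeated after 6 months. A third-group switch at month 12 would put that at month 18, after the last visit.

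**The case against.** **The shift is small and conservative.** At 0.91 of 0.25 SD the estimate moves by about 0.02 SD. With 12 practices of 20 the standard error is about 0.07 to 0.11 SD, so the shift is some 0.2 to 0.35 standard errors, toward no effect. This stands, and it limits the weight of the point. It does not rescue the analysis, because the size of the shrinkage is set by crossover and drop-out timing and not by any reason why scores might be missing.

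**LOCF is itself a departure from MAR.** This also stands. A reader might infer that LOCF says nothing at all about informative drop-out. That goes too far: it amounts to assuming that patients lost before the switch gain nothing from the intervention, and a result that survives this carries some information. But it is one crude and implausible scenario with no way to vary its severity.

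**The article is condensed.** A reader might infer that the trial has no valid check of MAR. The article cannot support this, since a fuller plan may hold further analyses. Likewise it does not say whether scores would be filled in after death. The point concerns only the rule that is stated.

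**The worst figures are unlikely.** The 0.85 end needs the 9/12/15 schedule, which sits badly with the per-protocol rule. Drop-out above 20% would exceed the article's stated maximum and is not used here.

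**Conclusion.** The point holds for the sensitivity analysis as stated. With 20% drop-out, even and completely at random, LOCF is expected to return about 0.91 of the true effect under the best-supported schedule and about 0.85 under the least favourable one, with 7% to 15% of intervention-period values being control scores. A gap from the primary result is thus expected from the design alone, which makes LOCF a poor test of MAR.

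Two stronger readings are not supported. The primary result is not biased by this rule: it uses no imputation and was unbiased in the check. Nor does LOCF manufacture a benefit: its bias is toward no effect, nil under a zero effect with equal drop-out, and negligible in the unequal drop-out scenarios tried. The figures rest on the assumed drop-out pattern, a constant effect and the unseen crossover schedule. The point deserves correction but does not threaten the primary inference.

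**What to change.** Replace LOCF with multiple imputation from a model containing exposure, occasion, practice and patient. Add a prespecified range of delta shifts to the missing intervention-period MAI scores (for example 0 to 0.25 SD worse), and report the shift at which the conclusion changes. Do not impute after death. Justify the range before the treatment comparison is run; Trial status says analysis had only just started at submission. Anything added after results are known should be labelled post hoc.

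If LOCF is kept for comparability with other studies, carry values only within the same condition. A score last seen under control then stops at the crossover, and later visits stay missing and are handled by the mixed model. Report it as descriptive.

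The cost is a few sentences in the analysis plan and a few hours of programming, with no new data. The delta range is a judgement that has to be defended, and other controlled departures from MAR, such as pattern-mixture models, would serve as well.
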